# **Effect of Different Treatments on Dentin Hypersensitivity: A Randomized Clinical Trial**

## **Abstract**

The objective of this study is to investigate the effects of different categories of treatments for dentin hypersensitivity through a randomized clinical trial, using the following protocols: fluoride varnish (positive control, Duraphat – VF); solution containing crystalline bioactive ceramic (Biosilicate® – SS); self-etch adhesive system (Single Bond Universal – SB); and bioactive light-cured varnish (PRG – VB). A total of 192 teeth (48 per treatment) with exposed root surfaces presenting dentin hypersensitivity (without cavitation) will be treated in a randomized parallel study design. The degree of dentin hypersensitivity will be evaluated using the Visual Analog Scale (VAS) and the Computerized Visual Analog Scale (CoVAS), at baseline and after 7, 15, and 30 days, as well as 6 and 12 months post-treatment. Data will be subjected to appropriate statistical analyses. This study is expected to contribute to the understanding of the mechanisms of action of new desensitizing protocols and to provide an innovative and effective clinical approach for the management of dentin hypersensitivity.

**Keywords:** Tooth Wear; Dentin Desensitizing Agents; Dental Erosion; Clinical Trial

## **1. Introduction and Justification**

Dentin hypersensitivity (DH) is defined as a short, sharp pain arising from thermal, tactile, chemical, or osmotic stimuli. Among the mechanisms proposed to explain DH, the hydrodynamic theory assumes that external stimuli promote fluid movement within the dentinal tubules, resulting in contraction and expansion of odontoblastic processes, thereby stimulating nerve fibers at the dentin–pulp interface. This condition is closely associated with root exposure, with or without the presence of non-carious cervical lesions (NCCLs). Treatment options include surgical root coverage procedures, adhesive restorations in cases of cavitation, or the application of desensitizing agents when surgery or restorative procedures are not the treatments of choice. Desensitizing agents act either by obliterating dentinal tubules or by reducing nerve excitability; however, due to the multifactorial etiology of DH, their long-term effectiveness is limited. Currently, the literature identifies three main categories of products for the treatment of DH: fluoride varnishes, experimental bioactive solutions, and light-cured agents.

Fluoride varnishes account for a large portion of the protocols used, as they are capable of reducing or blocking fluid movement within dentinal tubules through the formation of calcium-phosphate precipitates. However, their long-term effectiveness may be limited, which has encouraged the development of alternative products designed to prolong the desensitizing effect.

Experimental solutions with bioactive potential, another category tested for DH management, include materials with a structure more closely resembling the mineral portion of teeth. Among these are crystalline bioactive ceramic solutions, such as biosilicates, which were proposed to promote hard tissue remineralization by calcium phosphate precipitation and hydroxyapatite formation. This property provides these materials with potential for tubule occlusion, dentin remineralization, and prevention of demineralization.

Considering the category of light-cured agents, universal adhesive systems provide a treatment option by sealing dentinal tubules and forming a hybrid layer, thereby neutralizing the hydrodynamic mechanism of hypersensitivity. In addition, a more recent product has been introduced to the dental market: a light-cured varnish containing surface pre-reacted glass particles capable of releasing fluoride. This bioactive technology allows multifunctional glass particles trapped within the polyacid matrix to release other ions, including strontium, borate, aluminum, silicate, and sodium. As a result, the product contributes to neutralizing dietary acids and remineralizing tissues, while also promoting tubule occlusion through polymerizable monomers.

Marto et al. (2019), in a meta-analysis evaluating randomized clinical trials with different DH treatments, concluded that only in-office treatments are effective in producing immediate reduction of hypersensitivity and may maintain their effect over time. However, further treatment protocols should be studied, with extended follow-up periods.

Therefore, conducting a study to evaluate new protocols for the reduction of DH through randomized clinical trial methodologies is warranted

## **2. Objectives**

The objective of this study is to evaluate the influence of different protocols for the treatment of dentin hypersensitivity. The null hypotheses to be tested are as follows: a) there will be no statistically significant difference in dentin hypersensitivity among the desensitizing protocols at each evaluation time point; b) there will be no statistically significant difference across evaluation time points when the same desensitizing protocol is assessed.

This research project will be submitted to the local ethics committee and registered in a clinical trial database (REBEC). The study is described in accordance with the CONSORT recommendations.

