## **3. Materials and Methods**

### **3.1 Experimental Design**

This will be a parallel, prospective, randomized clinical trial. Only the volunteers will remain blinded to the allocation group (single-blind design).

A sample of 192 teeth with exposed hypersensitive root dentin will be planned, with 48 teeth per group. The study factors will be: (1) desensitizing treatment at four levels

(Table 1): fluoride varnish (positive control, Duraphat – VF); solution containing crystalline bioactive ceramic (Biosilicate® – SS); self-etch adhesive system (Single Bond Universal – SB); and light-cured fluoride varnish (VL); and (2) evaluation times: baseline (prior to treatments), and 7, 15, and 30 days, as well as 6 and 12 months post-treatment. The response variables will be hypersensitivity assessment through the Visual Analog Scale (VAS) and the Computerized Visual Analog Scale (CoVAS).

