### 3.2 Sample Size Calculation and Patient Selection

Sample size was calculated based on a published study using Sigma Plot 12.0 software, with an expected mean difference in cervical dentin hypersensitivity levels (measured by VAS) of 0.210 after six months. Test details: significance level ( $\alpha$ ) = 0.05; test power ( $1-\beta$ ) = 0.80; dropout ( $\beta$ ) = 0.2. The final sample size was determined as 48 teeth per group.

Patients will be recruited from the undergraduate clinic of FOA-UNESP, aged between 20 and 70 years, with at least one root exposure, totaling 192 teeth with DH in non-cavitated root exposures (not requiring restoration), regardless of location in the dental arch. Teeth will be divided into three groups ( $n = 48$  teeth each) with a 5% significance level. Eligibility criteria are described in Table 2.

**Table 1.** Products to be used in the study and their composition according to the manufacturers

| Material                                                                                                                                                                                                                                                                          | Manufacturer                                  | Composition*                                                                                                                                                                           | Application*                                                                                                                                                                             |
|------------------------------------------------------------------------------------------------------------------------------------------------------------------------------------------------------------------------------------------------------------------------------------------|------------------------------------------------------|-----------------------------------------------------------------------------------------------------------------------------------------------------------------------------------------------|-------------------------------------------------------------------------------------------------------------------------------------------------------------------------------------------------|

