### 3.6 Statistical Analyses

The results of DMFT, VPI, GBI indices, and root exposure height will be presented descriptively. Correlation between the sensitivity assessment methods used (CoVAS and VAS) will be analyzed using Spearman's correlation coefficient. Comparisons among treatments at the same evaluation time and among time points within the same treatment will be analyzed using equality tests for two proportions, with a significance level of 5%.

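### The trial is sized on VAS at six months, but no scale, visit or contrast is primary and up to 60 between-product tests run at an unadjusted 5%

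*Protocol*

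**What the plan says.** - **Hypotheses (Protocol, Section 2).** Hypothesis (a) is that "there will be no statistically significant difference in dentin hypersensitivity among the desensitizing protocols at each evaluation time point". Hypothesis (b) says the same of time points within one product.
- **Design (Section 3.1).** The factors are "desensitizing treatment at four levels", one of them labelled the positive control, and time: "baseline (prior to treatments), and 7, 15, and 30 days, as well as 6 and 12 months post-treatment". The response variables are VAS and CoVAS, and neither is called primary.
- **Sample size (Section 3.2).** The calculation is made "with an expected mean difference in cervical dentin hypersensitivity levels (measured by VAS) of 0.210 after six months", at 5% significance and 80% power, and gives 48 teeth per group. It does not say which two products the difference refers to.
- **Analysis (Section 3.6).** "Comparisons among treatments at the same evaluation time and among time points within the same treatment will be analyzed using equality tests for two proportions", at a significance level of 5%. The section states no overall test across the four products, no primary scale, visit or contrast, and no control of error over the set of tests.

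**The concern.** A two-proportion test compares two groups, so testing four products at one visit means testing them in pairs. Hypothesis (a) is set at every visit and the tests run on both scales, each at the full 5%. Any one significant result would contradict hypothesis (a) as worded and could be reported as one product beating another.

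The sample size calculation implies a single endpoint, VAS at six months. Because Sections 2 and 3.6 do not name it, a difference on CoVAS at day 15 would carry the same formal weight as the comparison the trial was sized for. The positive control likewise has no special role in any comparison.

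**Working it through.** **Inputs.** From the Protocol: four products, five post-treatment visits and two scales (Section 3.1); 48 teeth per group, 80% power, 20% dropout (Section 3.2); 5% per test (Section 3.6). Section 3.2 also speaks of three groups; four is used here because 192 = 4 x 48. Assumed, because the Protocol does not give them: two-sided tests, all pairs compared, and the correlations between visits and between scales. Clustering of teeth within patients is not modelled.

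**The plan's own figure.** The 48 per group cannot be reproduced, because no SD is given. Solved backwards with a two-sided test of means, 48 evaluable teeth imply an SD of about 0.367 (0.210/0.367 = 0.57 SD). If 38 was inflated for dropout, 38/(1 - 0.2) = 47.5, rounded to 48, the SD is about 0.327.

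**Number of between-product tests.** Pairs: 4 x 3/2 = 6. Tests: 6 x 5 visits x 2 scales = 60. Expected false positives if no product differs: 60 x 0.05 = 3.

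**One visit, one scale.** The six pairs share arms, so 1 - 0.95^6 = 26.5% is too high. The exact value is the probability that the studentized range of four means exceeds 1.96 x √2, which is 20.3%. Simulated two-proportion tests with 48 per arm give about 21%.

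**All visits and scales, bounds.** If the ten visit-by-scale sets were independent: 1 - (1 - 0.203)^10 = 89.7%. If all 60 tests were independent: 1 - 0.95^60 = 95.4%. Neither should be quoted as the rate, because repeated measurements on the same teeth are correlated.

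**All visits and scales, simulated.** Chance of at least one false difference with no true difference, 48 teeth per arm, six pairs, five visits, two scales:

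| Visit correlation | Scale correlation | Two-proportion test | t-test |
|---|---|---|---|
| 0.5 | 0.7 | 83-85% | 77-78% |
| 0.7 | 0.7 | about 80% | about 67% |
| 0.9 | 0.9 | about 66% | 46-48% |

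The two-proportion values also depend on the unknown responder proportion. Proportions nearer 0 or 1 give slightly higher rates; at 0.9/0.9 the range is 65-71%.

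**Narrower readings.** VAS only, five visits, two-proportion test: 65%, 60% and 48% at visit correlations 0.5, 0.7 and 0.9. Only the three contrasts with control, compared as means: about 12.5% at one visit on one scale; over all visits and both scales 62%, 50% and 42% when both correlations are 0.5, 0.7 and 0.8.

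**Cost of control on one endpoint.** The approximate detectable difference in SD units at 80% power is d = (z for 1 - α/2 + 0.842) x √(2/n). The noncentral t gives slightly larger values:

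| Evaluable per arm | α per test | Approximation | Noncentral t |
|---|---|---|---|
| 48 | 0.05 | (1.960 + 0.842) x 0.2041 = 0.57 | 0.58 |
| 48 | 0.05/3 | (2.394 + 0.842) x 0.2041 = 0.66 | 0.67 |
| 48 | 0.05/6 | (2.638 + 0.842) x 0.2041 = 0.71 | 0.72 |
| 38 | 0.05 | 2.802 x 0.2294 = 0.64 | 0.65 |
| 38 | 0.05/3 | 3.236 x 0.2294 = 0.74 | 0.76 |
| 38 | 0.05/6 | 3.480 x 0.2294 = 0.80 | 0.82 |

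The 38 is 48 x 0.8 = 38.4, rounded down. At 0.58 SD and 48 per arm, power falls from 80% to about 65% (three contrasts) or 56% (six pairs). With 38 per arm and three contrasts it is about 53%. The adjusted rows use Bonferroni, so they bound the cost of Holm, Dunnett or Tukey.

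**The case against.** - **This could sit in a separate analysis plan.** In part that is right: the choice of adjustment method is often left there, and such a plan may exist. But the Protocol itself fixes the hypotheses, the type of test and the 5% level, and these do not match its own sample-size basis.
- **A false difference is more likely than not.** A reader might infer this outright. It holds only if all four products are equal, and only for some correlations, which the Protocol does not report. With t-tests and correlations of 0.9 it is below one half, as it is for VAS alone with the two-proportion test at 0.9.
- **Every pair will be tested.** This is inferred from the use of a two-sample test. Section 3.6 speaks only of comparisons among treatments, so 60 is an upper count.
- **Hypothesis (b) adds many more false positives.** It could bring up to 4 products x 15 visit pairs x 2 scales = 120 tests. They do not belong in a calculation that assumes no true difference, because all four products are given as treatments and change from baseline is expected. They enter none of the rates above.
- **A chance finding would change the care of patients who did well.** The documents do not support this. The provisions in Sections 3.3 and 3.4 for giving the best-performing product concern patients whose treatment was ineffective.
- **Comparing only with the control changes the question.** This stands. Hypothesis (a) is framed among all products, so control contrasts are one option and not the only valid one.

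**Conclusion.** The point holds. The Protocol tests four products at each of five post-treatment visits on two unranked scales at an unadjusted 5%, while its sample size rests on one scale at one visit. The firmest figure is about 20% for six pairs at one visit on one scale, because it needs no assumption about correlations between visits or scales. It applies even if six-month VAS is read as the implied primary endpoint. The rates over all visits and scales are conditional on no product differing from another, on all pairs being compared, on independent teeth and on the assumed correlations. They show that the inflation is large, not its exact size. The change should be made before data are analysed.

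**What to change.** In Sections 2 and 3.6, declare VAS at six months, the endpoint already used for sizing, as primary. Control the familywise error at 5% over its between-product comparisons in one of two ways:

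- Holm or Dunnett for the three contrasts with the named positive control; or
- Holm or Tukey for all six pairs, if hypothesis (a) is to remain a statement among all products.

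Report the other visits, CoVAS and within-product changes as secondary, with estimates and 95% confidence intervals.

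**Cost.** The change alters wording but no visit or procedure. It does cost power. With 48 evaluable, independent teeth per arm, the detectable difference at 80% power rises from 0.58 to at most 0.67 SD (three contrasts) or 0.72 SD (six pairs). With 38 after the stated dropout it rises from 0.65 to at most 0.76 or 0.82 SD. Taking the unadjusted design as having 80% power at 48 evaluable per arm, Bonferroni would need about 65 (three contrasts) or 75 (six pairs) to restore it.

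These figures apply if VAS is compared as a mean, as in Section 3.2. Section 3.6 names a test of proportions, so the test for the primary endpoint must be reconciled with the sample-size basis. If proportions are kept, the responder cut-off and the expected proportions must be stated and the cost reworked.

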## **3. Materials and Methods**

### **3.1 Experimental Design**

This will be a parallel, prospective, randomized clinical trial. Only the volunteers will remain blinded to the allocation group (single-blind design).

A sample of 192 teeth with exposed hypersensitive root dentin will be planned, with 48 teeth per group. The study factors will be: (1) desensitizing treatment at four levels

(Table 1): fluoride varnish (positive control, Duraphat – VF); solution containing crystalline bioactive ceramic (Biosilicate® – SS); self-etch adhesive system (Single Bond Universal – SB); and light-cured fluoride varnish (VL); and (2) evaluation times: baseline (prior to treatments), and 7, 15, and 30 days, as well as 6 and 12 months post-treatment. The response variables will be hypersensitivity assessment through the Visual Analog Scale (VAS) and the Computerized Visual Analog Scale (CoVAS).

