| Duraphat (VF)                                                                                                                                                                                                                                                                     | Colgate-Palmolive Company®                           | NaF 5% (22,600 ppm); colophony; ethanol; shellac; mastic; saccharin; flavoring; white wax; beeswax                                                                                            | A thin layer will be applied with a microbrush on the clean and dry surface; stable for 10 minutes.                                                                                             |
| Biosilicate® (SS)                                                                                                                                                                                                                                                                 | Vitrovita, Institute of Innovation in Vitroceramics® | Solution 1:10 of P (1–10 µm) and distilled water. Elements: P 2 O 5 ; Na 2 O; CaO; SiO 2                                                          | A thin layer will be applied with a microbrush on the clean and dry surface. The solvent will be evaporated for 5 s and then rubbed for 20 s. Finally, light curing will be performed for 10 s. |
| Single Bond Universal (SB)                                                                                                                                                                                                                                                        | 3M ESPE, Dental Products®                            | Ethanol; BISGMA; Silane treated with methacrylate; HEMA; Copolymer of acrylic and itaconic acid; UDMA; Water; Dipentaerythritol pentaacrylate phosphate; Initiator                            | A thin layer will be applied with a microbrush on the clean and dry surface. The solvent will be evaporated for 5 s and then rubbed for 20 s. Finally, light curing will be performed for 10 s. |

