| PRG Barrier Coat (VB)                                                                                                                                                                                                                                                             | Shofu INC.®                                          | S-PRG (3.0 µm) based on distilled water; fluoroboroaluminosilicate glass; methacrylic acid monomer; phosphonic acid monomer; Bis-MPEPP; carboxylic acid monomer; TEGDMA; initiator and others | A drop of activator will be mixed in the capsule. The mixture will be applied with a disposable brush in a thin layer on the surface, dried for 3 s, and then light cured.                      |
| Abbreviations: TMP (sodium trimetaphosphate nanoparticle); TEGDMA (triethylene glycol dimethacrylate); BISGMA (bisphenol A diglycidyl ether dimethacrylate); HEMA (2-hydroxyethyl methacrylate); UDMA (urethane dimethacrylate); Bis-MPEPP (bisphenol A polyethoxy methacrylate). |                                                      |                                                                                                                                                                                               |                                                                                                                                                                                                 |
| *According to manufacturers: de Melo Alencar et al. (2019)  ; Fujimoto et al. (2010)  .                                                                                                                                                                         |                                                      |                                                                                                                                                                                               |                                                                                                                                                                                                 |

**Table 2.** Inclusion and exclusion criteria for patients

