|                                                                                                                                                                                                             | -Use of analgesics or anti-inflammatory drugs                                             |

Following the guidelines of the Federal Council of Dentistry for clinical care during the COVID-19 pandemic, the following protocol will be adopted: patients will be scheduled at staggered times to avoid crowding; 70% alcohol solution will be available in waiting areas for hand hygiene; face masks will be mandatory; the clinical environment will be disinfected between appointments from the least contaminated to the most contaminated areas (reflector handle, chair, stool, assistant cart surface, and dental unit, respectively); PVC barriers will be applied to contact surfaces (mechanical buttons, reflector handles, chair backrests and armrests, stool backrest, handpieces, three-way syringe body, and suction tips); all instruments will be disinfected with enzymatic detergent and sterilized.

Researchers will wear impermeable disposable gowns, disposable caps, protective goggles, surgical masks (for non-aerosol procedures), PPF or N95 masks (for aerosol-generating procedures), face shields, and gloves, all changed after each appointment. Regarding air-jet sensitivity testing in root exposures, relative isolation with cotton rolls will be used, and adjacent teeth will be covered with insulating tape (Isotape, TDV Dental, Pomerode, Santa Catarina, Brazil). The stimulus will consist of an air jet delivered by a three-way syringe positioned 1 cm from the cervical region for a maximum of 2 s. Immediately afterward, patients will indicate sensitivity level on the VAS, which consists of a 10 cm horizontal line where pain is scored from 0 to 10 points: 0 = no pain, 1–3 = mild pain, 4–6 = moderate pain, and 7–10 = severe pain. Patients will mark a vertical line across the horizontal scale to indicate DH intensity. The distance in mm from the zero endpoint will be measured with a millimeter ruler. Teeth with at least grade 3 sensitivity on the VAS will be included.

After selection, each patient will receive and sign an informed consent form (in duplicate), detailing study objectives and procedures.

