### 3.3 Baseline Assessments

Patients' oral conditions will be assessed through the Decayed, Missing, and Filled Teeth Index (DMFT), Visible Plaque Index (VPI), and Gingival Bleeding Index (GBI). Next, with a millimeter probe, root exposure height will be measured as the distance between the apical limit of the cemento-enamel junction and the highest point of the free gingival margin. At this stage, the values will not be classified; scores will be established only after the complete sample has been obtained.

Root exposure height and sensitivity scores by VAS will be stratification variables in the randomization process. The tooth will be considered the sampling unit. Eligible teeth will be entered into an Excel spreadsheet according to root exposure height and mean sensitivity score. To ensure a homogeneous distribution of these two factors across study groups, teeth will be ordered by sensitivity scores and divided into two clusters: one with lower scores and the other with higher scores. These clusters will then be subdivided by smaller/larger exposure size, resulting in four groups: (a) lower sensitivity and smaller exposures, (b) lower sensitivity and larger exposures, (c) higher sensitivity and smaller exposures, and (d) higher sensitivity and larger exposures. This stratified randomization method was based on another parallel clinical trial. Stratification will be performed approximately every 48 selected teeth for methodological feasibility.

In cases where experimental treatments do not reduce dentin hypersensitivity, patients will receive the product with the best performance to avoid further damage.

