### 3.4 Clinical Procedures

After baseline assessments, a lip and cheek retractor will be placed. The tooth receiving the desensitizing agent will be isolated with cotton rolls and dried with an air jet, with moisture controlled by suction. The assigned product will be applied in two layers with a microbrush and left on the surface for 10 minutes. Light-cured products will be photoactivated for 10 s (LED Radium-cal, SDI Brasil Indústria e Comércio LTDA, São Paulo, Brazil). Afterward, cotton rolls and the retractor will be removed.

At the end of the study, if experimental treatments are ineffective in reducing dentin hypersensitivity, patients will be treated with the product that shows the best results to avoid further complications.

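### The single-blind claim is not secured by the described procedures: some teeth get a curing lamp and others do not, no masking step is given, and both outcomes are rated by the patient

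*Protocol*

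**What the plan says.** Section 3.1 limits blinding to the patient: "Only the volunteers will remain blinded to the allocation group (single-blind design". Operator and assessor are openly unblinded.

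Both response variables come from the patient. Section 3.2 has the patient mark the VAS line and record CoVAS discomfort with a hand-operated potentiometer.

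On handling, Section 3.4 says: "Light-cured products will be photoactivated for 10 s". It does not name those products. Table 1 (Section 3.2) gives the application for each arm:

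- Duraphat: "A thin layer will be applied with a microbrush on the clean and dry surface; stable for 10 minutes". No lamp is mentioned.
- Biosilicate and Single Bond Universal, in identical wording: "Finally, light curing will be performed for 10 s".
- PRG Barrier Coat: an activator is mixed in the capsule, then "The mixture will be applied with a disposable brush in a thin layer on the surface, dried for 3 s, and then light cured".

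Section 3.3 sets the unit: "The tooth will be considered the sampling unit". Section 3.2 asks for one or more root exposures per patient and sets no upper limit. Before baseline, "each patient will receive and sign an informed consent form (in duplicate), detailing study objectives and procedures".

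**The concern.** On a pain scale that the patient completes, blinding the patient is what stops expectation from entering the outcome. Here it is the only blinding planned, so if it fails no blinded rater remains. The protocol asserts the blinding but describes nothing that would produce it: no sham light, no eye cover, no preparation out of sight. Handling differs between arms in ways a patient can notice. Because teeth rather than patients are allocated, the same person may receive two different procedures. Any expectation effect would then be mixed with the treatment effect in contrasts between lamp and no-lamp arms. A larger sample would not remove it, and no later analysis can restore masking lost at treatment.

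**Working it through.** The protocol gives no figure on this point, so there is none to reproduce. The check sets the passages side by side and counts what follows.

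**1. Lamp by arm**

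| Arm | Table 1 | Section 1 |
|---|---|---|
| Duraphat (VF) | no lamp | fluoride varnish |
| Biosilicate (SS) | lamp, 10 s | bioactive solution, listed apart from light-cured agents |
| Single Bond Universal (SB) | lamp, 10 s | light-cured agent |
| PRG Barrier Coat (VB) | lamp, time not stated | light-cured agent |

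The Biosilicate row is the only conflict. Section 1 names three product categories, "fluoride varnishes, experimental bioactive solutions, and light-cured agents", and places only the universal adhesive and the pre-reacted glass varnish in the last. The Biosilicate application text in Table 1 repeats the Single Bond text word for word, while its composition entry lists no monomer or initiator. Section 3.4 does not settle the matter.

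**2. Contrasts that differ by lamp**

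- All pairs among four arms: 4 × 3 / 2 = 6.
- Biosilicate cured (one arm against three): 1 × 3 = 3 of 6, all of them against Duraphat.
- Biosilicate not cured (two against two): 2 × 2 = 4 of 6, namely VF–SB, VF–VB, SS–SB and SS–VB. VF–SS would not differ by lamp.

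So at least three contrasts are exposed on either reading, but which ones depends on the reconciliation.

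**3. Can one patient meet both procedures?**

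Nothing prevents it. The protocol does not give the number of teeth per patient, so how often it happens is unknown. As an illustration only, assume each of m study teeth in a patient is allocated independently, 1/4 to each arm. The chance of having at least one lamp tooth and one no-lamp tooth is:

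- Biosilicate cured: 1 − (1/4)^m − (3/4)^m
- Biosilicate not cured: 1 − 2 × (1/2)^m

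| m | cured | not cured |
|---|---|---|
| 1 | 0 | 0 |
| 2 | 1 − 0.0625 − 0.5625 = 0.375 | 1 − 0.5 = 0.50 |
| 3 | 1 − 0.0156 − 0.4219 = 0.56 | 1 − 0.25 = 0.75 |
| 4 | 1 − 0.0039 − 0.3164 = 0.68 | 1 − 0.125 = 0.875 |

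Stratified allocation would change these values somewhat. The point is only that a mixed experience would be common among patients with several study teeth, if there are many such patients.

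**4. Other cues**

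In Table 1, only the PRG coat needs an activator mixed in its capsule, and only Duraphat lists saccharin and flavoring. Biosilicate and Single Bond have a rubbing step that the other two lack. The brush is not a safe cue: Table 1 gives the PRG coat a disposable brush, but Section 3.4 specifies a microbrush and a 10-minute dwell for every product.

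**The case against.** The strongest reply is that noticing a procedure is not knowing the allocation. Section 3.1 claims blinding to the group. A lamp does not name a product, and two or three arms share it. A patient with one study tooth has nothing to compare. The consent form is not among the documents at hand, and a form that details procedures need not tie each procedure to an arm. Several teeth in different arms is an inference from the design, not something the protocol states. All of this stands. It shows that blinding may survive in some patients, but not that the plan protects it.

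Four stronger readings are tempting, and the documents do not support them:

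- *Patients are unblinded.* The text shows that masking is not secured, not that it fails.
- *Only the control lacks the lamp, so the bias falls exactly on the comparisons with Duraphat.* This relies on the Biosilicate row of Table 1, which Section 1 contradicts.
- *Patients will favor the newer product.* That presumes they know which one it is.
- *The bias can be stated as a share of the planned 0.210 VAS difference, or as a false-positive rate.* The documents give no expectation shift, no unit for 0.210 and no standard deviation, and Section 3.6 plans tests of proportions rather than means. Any such percentage would only restate the assumed shift.

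**Conclusion.** The point holds in this form: the patient blinding claimed in Section 3.1 is not secured by the procedures in Section 3.4 and Table 1, and it is the only protection for two self-rated outcomes. Between three and four of the six pairwise contrasts differ by use of the lamp, depending on how the Biosilicate contradiction is resolved. The size and direction of any resulting bias cannot be derived from the documents. The conclusion rests on the absence of any masking step and on allocation by tooth without a cap or a same-arm rule. It does not need patients to identify the product, or any particular number of teeth per patient. The open operator and assessor are declared, and are not a contradiction. The trial can proceed, but the masking step or the claim should be changed, because masking belongs to the conduct of treatment and cannot be supplied at analysis.

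**What to change.** In Section 3.4, add a masking step for all four arms: block the patient's view, for example with an eye cover or opaque glasses, during preparation and application. For teeth whose product is not photoactivated, hold the lamp in place for the same 10 s without curing. Each product's application stays as assigned. The view must be blocked in every arm: an opaque cap on the lamp alone would hide the light and so still separate sham from real curing.

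Reconcile Table 1 with Section 1 on whether Biosilicate is light-cured, so that it is clear which teeth receive the sham lamp.

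If masking is not adopted, qualify the single-blind statement in Section 3.1 and report contrasts between lamp and no-lamp arms as not reliably blinded on a self-rated outcome.

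The cost is an eye cover and a few seconds per tooth; the alternative costs only wording. Residual cues, such as the taste of Duraphat and the rubbing step, may remain in either case and should be acknowledged.
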